## Colonoscopy: Zimbabwe

An intravenous injection of a single dose of 600 mg benzylpenicillin will be given in patients presenting for colonoscopy, 10 – 15 minutes before the procedure. Luminal fluid from the right side of the colon will be aspirated between 20 and 40 mins after benzylpenicillin administration. This fluid will be centrifuged, stored, and shipped to Imperial College where the assays for the presence of benzylpenicillin, which will indicate reverse permeation, will be performed. This sub-study is directed at understanding whether the degree of barrier loss in environmental enteropathy is sufficient to permit leakage of antibiotics into the right colon. Penicillin was selected as it is a narrow-spectrum antibiotic which would not be expected to cause significant microbiome disruption in these healthy volunteers, which might be an ethical concern. A recent study
^
37
^ showed that antibiotic secretion into bile can modulate the microbiota during cardiac surgery, but this is a situation where gut hypoperfusion is well known to drive barrier failure. Such effects have not, to our knowledge, been shown in EE.

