### Study aims

Aim 1: Evaluate a novel portfolio of stable isotope-based tools for evaluating carbohydrate and protein digestion and amino acid absorption.

Aim 2: Test a novel non-invasive fluorescence sensor-based tool for real-time evaluation of gut permeability.

Aim 3: Characterise the microbiome and metabolome across well characterised and novel physiological sites (duodenal aspirate, duodenal mucus, duodenal tissue, stool, plasma, urine).

Aim 4: Quantify systemic and intestinal inflammation using established biomarkers of EE, immune cell phenotyping, epithelial PRR expression, and in vitro epithelial barrier models.

Aim 5: Determine if antibiotics, given intravenously, permeate into the gut lumen in sufficient quantities to modulate the microbiota.

All of these will be correlated with histological mucosal morphometry, lactulose permeation, and established biomarkers of EE.

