### Study strengths and limitations

•A study of 80 adults with EE and 20 controls will develop novel analytical tools to demonstrate their viability and effectiveness for the assessment of gut functional capacity compared with current ‘gold standards’.•This study will inform future work on EE disease assessment and in treating children with severe acute malnutrition (SAM) and/or stunting.•These novel tools will have practical applications in clinical assessments not only in EE but other conditions that affect gut functional capacity allowing better understanding of the underlying mechanisms of different diseases.•A limitation of this study is the lack of country-specific controls in whom the same assays would be performed for comparison.•Including adults only in this study limits the applicability of some of the analytical methods when designing a child-based study due to smaller sample volumes.•The data will be generated over the course of a single 3-day protocol; analysis of longitudinal changes will require additional studies.

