### Study population

The initial study will be conducted in 80 adults from a population in Lusaka, Zambia, where our previous studies have demonstrated that EE is virtually ubiquitous in adults and children.
^
32
^ Additionally, 20 controls living in high socioeconomic status (SES) residential areas (Rhodes Park, Longacres, Kabulonga, Ibex Hill, Chelston, Avondale, Sunningdale, Roma, Chamba Valley, Lilayi, New Kasama and others) within Lusaka will be included. A further 20 patients attending for routine colonoscopy (for diagnostic purposes) in Harare, Zimbabwe will be enrolled for the antibiotic permeation study. As these participants will already be booked for colonoscopy they will be drawn from higher socio-economic groups.

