### Inclusion and exclusion criteria

This study will include and exclude participants following the criteria shown in
Table 2.

**Table 2. T2:** Inclusion and exclusion criteria.

Inclusion criteria	Exclusion criteria
• In Lusaka, only residents of Misisi compound and high SES residential areas, while in Harare, only patients who have been referred for a colonoscopy.	• This study will not include any individuals taking medication for type II diabetes.
• Only adults from high socio-economic status (i.e., living in detached houses with indoor flush toilets, tiled floors, separate kitchens with running water and indoor stoves, and own at least one vehicle) will be included in Harare and in the Zambian control group.	• Any contra-indication to study procedures including endoscopy, such as likely to cause problems with sedation (e.g., oropharyngeal anomaly, previous adverse reaction) or biopsy (e.g., bleeding diathesis).
• Participants of either sex will be included in the study.	• Pregnant or lactating.
• Participants aged between 18 and 65 years old.	• Currently taking any anticoagulants.
• Only participants who are able and willing to undergo HIV testing.	• Having renal failure or liver failure (any major organ system).
• Able and willing to give written, informed consent will be included.	• Any underlying condition, other than HIV, which in the opinion of the investigator would put the subject at undue risk of failing study completion or would interfere with analysis of study results.
	• Participants will be temporarily excluded from study procedures if they have had diarrhoea (by self-report) in the preceding month, and have taken antibiotics, non-steroidal anti-inflammatory drugs, and/or proton pump inhibitors in the preceding month until disqualifying condition has elapsed.

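### The Harare sub-study is said to test antibiotic leakage in environmental enteropathy (EE), but EE is neither selected for nor described as measured there, so Aim 5 needs a narrower statement

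*Protocol article*

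**What the plan says.** **Purpose.** The Study aims section gives Aim 5 as: "Determine if antibiotics, given intravenously, permeate into the gut lumen in sufficient quantities to modulate the microbiota". The Colonoscopy: Zimbabwe section states the purpose in terms of the disease: "whether the degree of barrier loss in environmental enteropathy is sufficient to permit leakage of antibiotics into the right colon". The Study design section is more modest. It describes exploring how far antibiotics pass from the circulation into the gut, with caecal fluid used to quantify this. Table 1 describes the Aim 5 outcome as a technique for assessing reverse permeation.

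**Population.** "A further 20 patients attending for routine colonoscopy (for diagnostic purposes) in Harare, Zimbabwe will be enrolled for the antibiotic permeation study". The Study population section adds that "they will be drawn from higher socio-economic groups". Table 2 sets one housing-and-assets definition of high socio-economic status (SES) and says that only adults meeting it "will be included in Harare and in the Zambian control group".

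**Measurements.** The Colonoscopy section describes one right-colon aspirate, taken after a single intravenous dose of benzylpenicillin and assayed for that drug. Table 4 and the Antibiotic analysis section list only the antibiotic assay for this fluid. Duodenal biopsy, sugar and fluorescein permeability testing, and stool and blood collection are described under Clinical investigations: Zambia.

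**Linkage.** The closing sentence of Study aims and the Aim 6 row of Table 1 commit all aims to comparison with duodenal morphometry, lactulose testing and EE biomarkers.

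**The concern.** The stated question is about EE, but nothing described for Harare identifies who has EE or how severe it is, and there is no second group to compare. If benzylpenicillin is found, the result cannot be credited to EE barrier loss. If it is not found, that does not show that EE barriers hold. The promised comparison with histology, lactulose permeation and biomarkers has no Harare data to draw on.

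At stake is what may be concluded from one of the five listed aims. As worded, the Colonoscopy section invites a reader to treat the result as evidence about EE whichever way it falls.

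**Working it through.** **1. Purpose against design**

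| What the stated purpose needs | What is described for Harare |
|---|---|
| Participants with EE, or a range of EE severity | High-SES colonoscopy patients; EE is not an entry condition |
| A measure of EE or of barrier loss | None described |
| A comparison group | None; one group of 20 |
| Histology, lactulose and biomarker data for the Aim 6 comparison | None described; the only research sample is one colonic aspirate |
| Evidence bearing on microbiota modulation | Luminal benzylpenicillin only |

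**2. Is there a sample size basis that implies a contrast?** No. The Sample size estimation section contains two calculations, and both reproduce.

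- Breath test: (20.29 − 16.02)/5.29 = 0.81. A one-sided 5% t-test with 80% power needs 19.7, so 20 per group, as stated.
- LPS: (481 − 192)/√((408² + 113²)/2) = 289/299.4 = 0.965. A two-sided test needs 17.9, so 18 per group, as stated.

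Neither concerns the antibiotic sub-study. The 20 in Harare has no stated precision or power target to reproduce.

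**3. What one group can identify.** Let π be the unknown share of the 20 who have EE, and let p₁ and p₀ be the detection probabilities with and without EE. The data estimate only

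p = π·p₁ + (1 − π)·p₀.

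The question concerns p₁, or p₁ − p₀. One equation with three unknowns does not give either. The documents give no value for π in Harare, so the range has to be shown.

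- *Nothing detected (0/20).* The exact 95% upper limit for p is 1 − 0.025^(1/20) = 16.8%. Because π·p₁ ≤ p, the limit on p₁ is 0.168/π. At π = 1 this is 16.8%. At π = 0.5 it is 0.168/0.5 = 33.7% (from the unrounded 0.1684). At any π of 16.8% or less there is no limit, so 0/20 would be compatible with leakage in every person with EE.
- *Detected in half (10/20).* Take p = 0.5 and assume π = 0.5. Then p₁ = 1 with p₀ = 0 fits exactly, and so does p₁ = 0 with p₀ = 1. Even the sign of the contrast is undetermined.

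A larger sample narrows the interval for p but leaves the same single equation.

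**4. What 20 patients can estimate.** The detection proportion in high-SES colonoscopy patients, with exact (Clopper-Pearson) 95% intervals:

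| Detected | 95% interval |
|---|---|
| 0/20 | 0 to 16.8% |
| 10/20 | 27.2 to 72.8% |
| 20/20 | 83.2 to 100% |

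The distribution of luminal concentration can also be described. These intervals show what the sub-study can deliver; they are not a measure of the defect.

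**The case against.** The strongest reply is that the sub-study is exploratory and that parts of the article already describe it modestly. The Study design section asks only about the extent of leakage and says it will be quantified, and Table 1 calls it a technique. One group of 20 can address that. This stands, and it is why the remedy is rewording and not redesign.

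A second reply is that Table 4 marks stool, plasma and biopsy assays as applying to all participants, which could literally include Harare. This leaves some ambiguity, but no collection of those samples in Harare is described. The listed limitation about missing country-specific controls does not help either, because what Harare lacks is identified EE and any comparator.

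Stronger readings are tempting, and the documents do not support them:

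- *That Harare enrols people defined as free of EE.* The article writes "A study of 80 adults with EE and 20 controls" and applies the same SES criterion to those controls and to Harare, so a reader might infer this. But the criterion describes living conditions, and nowhere are high-SES adults said to be without EE. The supportable statement is that EE status in Harare is unselected and not described as measured.
- *That Aim 5 can answer nothing.* The narrower question remains answerable in this population.
- *That the microbiota part fails for want of sequencing or a threshold.* Whether drug reaches "permeate into the gut lumen in sufficient quantities to modulate the microbiota" could be judged from luminal concentration, and a threshold is detail an article may leave to the full protocol.
- *That choosing penicillin contradicts the aim.* The choice is given an ethical reason. A probe drug need not itself disturb the microbiota for its permeation to be measured.
- *That the protocol commits to reading detection as EE barrier loss.* It says only that presence indicates reverse permeation; no such decision rule is written.

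**Conclusion.** The point holds in this limited form. The EE purpose in the Colonoscopy: Zimbabwe section, and the blanket comparison in Study aims and Table 1, do not match who is enrolled in Harare and what is described as measured there. Leakage, or its absence, cannot be attributed to EE, and no sample size changes that. The estimable quantities are a concentration distribution and a detection proportion among 20 high-SES colonoscopy patients.

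A related wording slip is that the section says penicillin "would not be expected to cause significant microbiome disruption in these healthy volunteers", although the participants are patients referred for diagnostic colonoscopy.

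This rests on reading the article as complete about which samples Harare provides. If the full protocol collects EE measures there, the article should say so, and the finding would shrink to the lack of a comparator. The matter should be fixed, but it is confined to a separate exploratory sub-study. The data on 80 adults and 20 controls in Lusaka are untouched.

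**What to change.** 1. Restate Aim 5, and the purpose sentence in Colonoscopy: Zimbabwe, in line with the Study design section: an exploratory estimate of benzylpenicillin concentration, and of the proportion with detectable drug (exact 95% interval), in right-colonic fluid of high-SES adults referred for colonoscopy.
2. Remove the inference about EE barrier loss. Limit any statement on the microbiota to what luminal concentration can support.
3. Exclude Aim 5 from the comparison with histology, lactulose and biomarkers, both in the closing sentence of Study aims and in the Aim 6 row of Table 1.
4. Describe the Harare participants as patients referred for colonoscopy.

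Opening Harare to other SES groups and reporting by group is not a substitute, because it would still measure no EE.

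The cost is rewording and a narrower conclusion for Aim 5. No participants, samples or procedures are added.

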## Sample handling

Samples for safety analysis (differential blood count using the Sysmex XP300™ automated haematology analyser (Sysmex UK Ltd., Milton Keynes, UK) and prothrombin time using the HumaClot Junior (HUMAN Diagnostics Worldwide, Wiesbaden, Germany)) will be processed immediately; excess samples will be retained as backup, but destroyed once the study is complete. Samples for research assays (
Table 4) will be analysed immediately or stored at appropriate temperatures (usually -80°C). Blood samples from Day 2 (9 mL) will be centrifuged (2,300
*g* for 5 minutes at 4°C) to separate plasma from buffy coat cells (enriched for immune cells) and red blood cells; plasma will be aliquoted and stored at -80°C and buffy coat cells will be treated to lyse red blood cells, fixed, washed, re-suspended in cell preservation media, and cryopreserved gradually to -80°C using cell freezing containers to maintain cell integrity. On day 3, blood collected at different time intervals in lithium heparin (
Table 4) will be centrifuged under the same conditions to separate plasma which will be aliquoted and stored at -80°C. Stool samples collected on days 2, 3 and 4 will be aliquoted and stored at -80°C. All saliva samples collected on days 2 and 3, all urine and stool samples collected on days 2, 3, and 4 will also be aliquoted and stored at -80°C. All breath samples that will be collected on days 2 and 3 will be stored at room temperature until analysis. All cryo-stored samples will be retained until batch analyses at either TROPGAN or may be shipped to the relevant external laboratories for analyses (shown in
Table 4). For sample types being shipped for analyses at external laboratories, an aliquot of each will be retained at TROPGAN wherever possible; these aliquots will act as a backup in case of analytical failures, or storage failures during transport to another laboratory.

**Table 4. T4:** Summary of laboratory analytical methods.

Sample Type	Assays	Methods	Study participants	Time-points
Stool	Microbiome sequencing	Illumina HiSeq, MinION	All	Baseline
	Barrier integrity and function	Epithelial cell co-cultures		Baseline or Day 2
	Biomarkers	ELISA		Baseline
	Immune signalling assays	Reporter cell line co-culture		Baseline or Day 2
	Dynamic proteomics	LC-MS/MS		Day 3, Day 4
	Metabolic phenotyping	NMR spectroscopy		Day 2, Day 3
Urine	Metabolic phenotyping	NMR spectroscopy	All	Baseline
	Targeted isotope analysis	LC-MS/MS		Day 1, Day 2
Saliva	Body Composition	FTIR	All	Day 1, Day 2
Biopsies	Histology and morphometry	Microscopy	All	Endoscopy samples
	Enzymes and transporters	Immunofluorescence		Endoscopy samples
	Pattern recognition receptor expression	Immunofluorescence, Immunohistochemistry		Endoscopy samples
	Dynamic proteomics	LC-MS/MS		Day 3 samples
Duodenal aspirates	Microbiome sequencing	Illumina HiSeq, MinION	All	Endoscopy samples
	Metabolic phenotyping	NMR spectroscopy		Endoscopy samples
	Dynamic proteomics	LC-MS/MS		Endoscopy samples
	Amino acid uptake in microbiota	LC-MS/MS		Endoscopy samples
	Stable isotope measurement	LC-MS/MS		Endoscopy samples
Plasma	Stable isotope measurement	LC-MS/MS	All	Multiple measurements
	Biomarkers	ELISA, Luminex		Baseline or Day 3
	Barrier integrity and function	Epithelial cell co-cultures		Baseline or Day 3
	Immune function assays	Reporter cell line co-culture		Baseline or Day 3
	Metabolic phenotyping	NMR spectroscopy		Day 2, Day 3
Buffy Coats	Innate and adaptive immune cells	Flow cytometry	All	Baseline
Whole blood	Haematology	Differential cell counts, coagulation	All	Baseline or Day 3
Breath tests	Stable isotope measurement	Infra-red isotope analyser	All	Multiple measurements
Colonic aspirates	Antibiotic assays	LC-MS, HPLC	Aim 3 only	Single aspirates per procedure

ELISA - Enzyme Linked Immunosorbent Assay; LC-MS/MS - liquid chromatography tandem mass spectrometry.

## Clinical assessments

### Permeability analysis

The permeability will be measured by the appearance in the blood of fluorescein ingested orally and through use of a multi-agent urinary recovery assay. Fluorescein will be purchased from Sigma-Aldrich (46960-100G-F) and has a similar molecular size to lactulose (molecular weight of fluorescein = 332 g/mol, molecular weight of lactulose = 342 g/mol) and similar molecular radius (lactulose, 0.42 nm; fluorescein 0.5 nm). We have previously demonstrated that the rate and degree of permeation of fluorescein vary under different permeability conditions
^
38
^ and in patients with intestinal disorders.
^
39
^ Importantly, following permeation into the blood, fluorescein fluorescence is quantifiable using a fingertip probe similar to a pulse oximeter probe.
^
40
^ Hence, transcutaneous measurement (performed using a fingertip probe) of fluorescence from orally ingested fluorescein will be used to provide rapid, non-invasive assessment of permeability.

To complement these novel, non-invasive, fluorescent measurements, we will also assess permeability using the urinary recovery of five orally ingested sugar and dipeptide molecules (lactulose, rhamnose, D-xylose, 3-O methyl-D-glucose and glycyl sarcosine). Urinary recovery of these molecules will be quantified using mass spectrometry thereby permitting assessment of more traditional permeability measures (e.g. urinary lactulose recovery and lactulose: rhamnose ratio) as well as quantification of the permeation of multiple agents with different molecular weights. Together, these two approaches allow a comprehensive, minimally invasive assessment of intestinal permeability.

## Laboratory assessments

### Stable isotopes analysis

The
**
*non-radioactive
*
** stable isotope labelled amino acids are used to trace the digestion and absorption of protein (day 2) and bidirectional transmucosal amino acid flux (day 3). The labelling strategy is chosen to minimise isotopic crosstalk in the analysis and maximise the metabolic pools that can be sampled ethically. These include breath (
^13^CO
_2_), plasma (
^13^C /
^2^H amino acids), intestinal aspirates (
^13^C /
^2^H amino acids), and urine (
^13^C /
^2^H amino acids). Breath samples will be analysed using a Thermo Scientific™ Delta Ray™ Isotope Ratio Infrared Spectrometer (Thermo Fisher Scientific, Bremen, Germany) in the TROPGAN laboratory (breath
^13^CO
_2_) and
^13^C &
^2^H labelled amino acids analysed by a Agilent 1290 Infinity LC coupled to a 6560 triple quadrupole mass spectrometer (Agilent Technologies Inc., Cheadle, UK) in SUERC (
^13^C/
^2^H amino acid isotopologues).

### Metabolic phenotyping

Urine, stool, plasma, and duodenal aspirates will be analysed by Nuclear Magnetic Resonance spectroscopy (NMR). High-throughput
^1^H NMR spectra will be acquired using a 600MHz Bruker Avance III™ HD NMR spectrometer equipped with a 5 mm BBI Z-gradient probe, high-order shims, and automated tuning and matching (Bruker Biospin, Rheinstetten, Germany). Samples will be analysed in automation using standard pulse sequences with water suppression. For urine, stool, and duodenal aspirates, two experiments will be acquired: (1D)
^1^H NMR (noesygppr1d, standard Bruker pulse program), and (2D)
^1^H−
^1^H
*J*-resolved (
*J*-Res) experiment (jresgpprqf
). (1D)
^1^H CPMG (Carr–Purcell–Meiboom–Gill, cpmgpr1d) will also be acquired for plasma only. Each 1D spectrum will be automatically phased and baseline corrected, digitized, and imported into MATLAB for preprocessing and statistical modelling.

### Microbiome analysis

Stool samples, gastric and duodenal aspirates and intestinal biopsies will undergo nucleic acid extraction, library construction and whole metagenome shotgun sequencing at Imperial College London to identify taxonomic and functional composition of multi-site gastrointestinal microbiomes comparing standard short-read sequencing approaches (Illumina HiSeq™ (Illumina, San Diego, CA, USA)) with novel long-read approaches (MinION (Oxford Nanopore Technologies Ltd., Oxford, UK) and PacBio Sequel
^®^ (Pacific Biosciences Inc., Menlo Park, CA, USA)). An additional qPCR step will be performed to quantify the absolute abundance of bacteria by determining the total number of 16S rRNA gene copies. These results will also be compared across sequencing platforms. These sequencing efforts will be duplicated in parallel work in Lusaka to determine the ease of application to an African laboratory. Additional characterisation of microbial uptake of amino acids and conversion of L to D amino acids will also be carried out. Raw sequencing data will be analysed via established bioinformatics pipelines including DADA2 (for 16S rRNA genes), EPI2ME and MetaPhlAn3 (compositional), HUMAnN3 (functional) as with other data, these results will be compared with duodenal biopsy histology, lactulose permeation data, and biomarkers.

To evaluate microbial uptake of amino acids, the ratio of
^13^C &
^2^H labelled amino acids in bacterial cells derived from duodenal aspirates will be measured using mass spectrometry. This ratio will serve as an indicator for microbial usage of amino acids pathological leaked into the gut lumen from systemic circulation. In addition, a quantitative ultra-high pressure liquid chromatography mass spectrometry (UPLC–MS/MS) assay will be used to measure the concentrations of L- and D-amino acids in duodenal aspirates. The concentration of labelled D-amino acids will serve as an indicator of microbial consumption and usage of total amino acids content in the duodenum.

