**Figure 2. f2:**
[figure not shown]
Study schema illustrating sample collection across the 4-day study period. Schema showing each sample collection time point throughout study, Day 1; No samples will be collected; Day 2; 9 mL heparinised blood; 2 mL EDTA blood; 5 mL citrated blood; 11 mL Urine at 00 and 180 mins; 4-8 g of stool; 0.5-2 mL of saliva at 00 and 180 mins; and breath samples every 20 mins. Day 3: 9 mL of heparinised blood; intermediate 2 mL heparinised blood samples every 20 mins for 1 h and every 30 mins for the last 2 h; breath samples every 20 mins; 0.5-2mL of saliva at 00, 60, 120 and 180 mins; 7 mL of urine at 00 and 180 mins; 4-8 g stool; 8 duodenal biopsies and 1 duodenal brushing; Day 4; 2-4 g of stool and 11 mL of urine.

### Day 1

This will include the final consent interview, administration of a questionnaire by the study nurse, clinical examination, and anthropometry (including weight, height, impedance, and deuterium approaches to body composition). Urine and stool collection devices will also be given.

### Day 2

Participants will bring urine and stool samples with them. Before administration of the solutions, a saliva sample, 9 mL of blood will be collected in lithium heparin, 2 mL in EDTA and 4.5 mL in citrated blood collection tubes, respectively, by venepuncture. A drink (prepared as shown in
Table 3) of
^2^H
_2_O (deuterated water, 1 g
^2^H
_2_O per kg body weight) containing
^13^C-spirulina protein (1.25 mg kg
^−1^) and (
^2^H
_8_)-Phe (0.035 mg kg
^−1^ in 200 mL clean water) will then be given at, or close to, 08:00 followed by breath sample collection using a straw and Exetainer tube (Labco, UK) every 20 mins for the first 1 h and every 30 mins for the remaining 3 h. A saliva sample will be collected at 180 mins, and a urine sample collection at 180 mins (3 h). A second drink of
^2^H
_2_O (1 g
^2^H
_2_O per kg body weight) will be given at 180 mins (3 h). During these procedures, a multi-pass 24-hour dietary recall will be administered by the study nurse. At the end of the procedures, the participant will be asked to fast after midnight and given stool and urine collection devices in readiness for day 3 procedures.

**Table 3. T3:** Composition of test solutions.

Solution	Composition	Administration
Solution A	• Deuterated water (D _2_O) (1 mL per kg body weight), • ^13^C-spirulina protein (1.25 mg kg ^−1^), and • ( ^2^H _8_)-Phe (200 mg) in 200 mL water	Oral, given at the beginning of day 2 procedures

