Solution B	• Deuterated water (D _2_O) (1 mL per kg body weight)	Oral, given at the end of day 2 procedures
Solution C	• ^2^H _5_-Phe (0.6 μmol kg ^−1^), • 5,5,5- ^2^H _3_-Leu (1.2 μmol kg ^−1^) made up to 10 mL with sterile filtered normal saline	Day 3, given intravenously as slow bolus at beginning of procedures
Solution D	• ^2^H _5_-Phe (0.15 μmol kg ^−1^) • 5,5,5- ^2^H _3_-leucine (0.3 μmol kg ^−1^) made up to 20 mL in sterile filtered normal saline	Day 3, given intravenously as continuous infusion over 3 hours
Solution E	• ^13^C _6_-Phe (0.6 μmol kg ^−1^), • ^13^C _6_-Leu (1.2 μmol kg ^−1^), • 5 g lactulose, • 1 g rhamnose, • 0.5 g D-xylose, • 0.2 g 3-O-methyl D-glucose, • 200 mg sodium fluorescein, • 1.667 mg L-arginine-(guanidineimino- ^15^N _2_) HCl, • 1.0 g glycyl sarcosine in 200 mL water	Day 3, given orally as bolus at beginning of procedures
Solution F	• ^13^C _6_-Phe (0.15 μmol kg ^−1^) • ^13^C _6_-Leu (0.3 μmol kg ^−1^) made up to 600 mL in clean water	Day 3, given orally as sips every 20 mins

### Day 3

Following an overnight fast, an intravenous cannula will be introduced into both arms and 5 mL of blood will be collected into a lithium heparin tube via cannula. The fingertip probe will be clamped gently onto a fingertip, and continuous fluorescence recordings will begin. An intravenous bolus of
^2^H
_5_-phenylalanine (0.6 mmol kg
^−1^) and 5,5,5-
^2^H
_3_-leucine (1.2 mmol kg
^−1^) in 10 mL normal saline filtered through a 0.2 mm syringe filter (solution C) will be given over 2 mins, and an oral bolus of
^13^C
_6_-leucine (1.2 mmol kg
^−1^),
^13^C
_6_-phenylalanine (0.6 mmol kg
^−1^), 5 g lactulose, 1 g rhamnose, 0.5 g D-xylose, 0.2 g 3-O methyl-D-glucose, 200 mg fluorescein, 1.667 mg L-arginine-(guanidineimino-
^15^N
_2_) HCl and 1.0 g glycyl sarcosine (solution E) given. A continuous intravenous infusion of
^2^H
_5_-phenylalanine (0.15 mmol kg
^−1^) and
^2^H
_3_-leucine (0.3 mmol kg
^−1^) (solution D) will be commenced, at 5 mL h
^−1^, and sips of
^13^C
_6_-phenylalanine (0.15 mmol kg
^−1^) and
^13^C
_6_-leucine (0.3 mmol kg
^−1^) (solution F) administered as sips every 20 mins (prepared as shown in

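### The labelled D-amino-acid index is a raw concentration, so it mixes microbial conversion with dilution and with the amount of label in the duodenum; a D/(D+L) fraction should be reported beside it

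*Protocol article*

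**What the plan says.** The Microbiome analysis section defines two amino-acid indices on duodenal aspirates.

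- **Leakage ratio.** The ratio of 13C- to 2H-labelled amino acids in bacterial cells from the aspirate. Its reading is given as: "This ratio will serve as an indicator for microbial usage of amino acids pathological leaked into the gut lumen from systemic circulation". No isotopologue is named.
- **D-amino-acid index.** A UPLC–MS/MS assay will "measure the concentrations of L- and D-amino acids in duodenal aspirates", and then: "The concentration of labelled D-amino acids will serve as an indicator of microbial consumption and usage of total amino acids content in the duodenum". No denominator is given.

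Table 1 (Aim 3, microbiome item III) sets the outcome these serve: how able the microbial communities are to take up intestinal amino acids and to convert L-forms to D-forms.

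Table 3 gives the tracers. On Day 3, 2H5-Phe and 2H3-Leu are intravenous (Solutions C and D), while 13C6-Phe and 13C6-Leu are oral (Solutions E and F). Solution E is a 200 mL drink; Solution F, taken as sips, is "made up to 600 mL in clean water". On Day 2, Solution A contains 2H8-Phe, 13C-spirulina and deuterated water and is "Oral, given at the beginning of day 2 procedures"; a second deuterated-water drink follows. The aspirate is taken at endoscopy, after 240 minutes on Day 3.

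The Statistical analysis plan section compares all data with duodenal morphometry as the most direct measure of severity, and treats those comparisons as validation of the tools.

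**The concern.** The outcome is an ability to convert, which is a rate or a fraction. The stated indicator is an amount per volume of fluid. For the same microbial ability, a participant with more labelled substrate in the lumen has more labelled D-form, and a participant whose duodenal contents are more diluted has a lower concentration.

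The supply of label is not neutral here. It is set by absorption of the oral tracer and by leakage of the intravenous tracer, two functions that the Introduction and Figure 1 describe as impaired in enteropathy. If the index is then compared with villus morphometry, a malabsorption or leakage signal could be read as a microbial one. This is a matter of what the protocol states the index to mean, not of detail that a separate analysis plan would normally supply.

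**Working it through.** The documents give no numerical value for either index, so there is no stated figure to reproduce. The check is on how the index behaves.

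**Inputs from Table 3.** Oral Day 3 label per kg: Phe 0.6 + 0.15 = 0.75 µmol; Leu 1.2 + 0.3 = 1.5 µmol; total 2.25 µmol. Intravenous Day 3 label per kg: the same amounts, total 2.25 µmol. The infusion and sip figures are read here as totals. The Day 3 text gives these amounts in mmol; because the oral and intravenous amounts match in either unit, the fold-changes below do not depend on it.

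**Assumed inputs (illustrative).** Unabsorbed oral fraction u = 5% or 20%; leaked intravenous fraction l = 1% or 5%; conversion c = 2% of the luminal pool.

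**Supply.** Labelled D amount = c × 2.25 × (u + l).

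| l | u = 5% | u = 20% | Fold-change |
|---|---|---|---|
| 1% | 0.02 × 2.25 × 0.06 = 0.00270 | 0.02 × 2.25 × 0.21 = 0.00945 | 3.5 |
| 5% | 0.02 × 2.25 × 0.10 = 0.00450 | 0.02 × 2.25 × 0.25 = 0.01125 | 2.5 |

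(µmol/kg.) At a fixed fluid volume the concentration changes by the same factor. Under this model D/(D+L) is 2% in all four cells.

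**Dilution.** Concentration = D amount / V. If V doubles, the concentration halves. In D/(D+L) the volume cancels. Up to 200 + 600 = 800 mL is drunk on Day 3 before the aspirate, and the share still in the duodenum will vary between participants.

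**Is D/(D+L) free of absorption?** Not necessarily. The constant 2% above follows from applying conversion to the residual pool. Suppose instead that 2 of 100 labelled units are converted before absorption, that D-forms are not absorbed, and that 10% or 20% of the remaining 98 L units stay in the lumen:

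- 10% residual: L = 9.8, so D/(D+L) = 2/11.8 = 17%.
- 20% residual: L = 19.6, so D/(D+L) = 2/21.6 = 9%.

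The fraction nearly halves at identical conversion, while the D amount is unchanged. The fraction removes dilution, but removes absorption only if D- and L-forms are absorbed alike.

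**Leakage ratio.** With equal oral and intravenous doses, 2H/13C in the lumen = l/u. At l = 1%, it is 0.01/0.05 = 0.20 when u = 5% and 0.01/0.20 = 0.05 when u = 20%. Malabsorption therefore lowers it at constant leakage, even with correctly chosen isotopologues.

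**The case against.** **The concentration may be what was intended.** The quoted sentence speaks of usage of total amino-acid content. If 2% of a larger pool is converted, the microbes did convert more, and a higher concentration reports that correctly apart from dilution. This stands, and is why the concentration should be kept. It does not make the concentration a measure of ability, which is the Table 1 outcome.

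**The fraction is not a clean replacement.** The 17% versus 9% example stands, and it limits what the fraction can be said to show.

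**A reader might infer that the leakage ratio is invalid because 2H is also given by mouth on Day 2.** The documents do not support that. Oral 2H8-Phe differs in mass from intravenous 2H5-Phe; no 2H-labelled leucine is given by mouth; and Stable isotopes analysis says that labels were chosen to limit crosstalk and that isotopologues are measured. Deuterated water adds little at the relevant masses. Assume 2.0–2.2 g/kg in total, body water 50–60% of weight and no loss: enrichment p is about 0.30–0.40 atom% excess. With full incorporation over 9 hydrogen sites (8 for Phe), this gives about 2.6–3.5% at M+1 but only 2–5 × 10⁻⁶ at M+3 and 1–5 × 10⁻¹¹ at M+5.

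**A reader might compare doses.** At an assumed 60 kg, Day 2 oral 2H8-Phe is 19.2 µmol/kg by Table 3 (200 mg) or 0.20 µmol/kg by the Day 2 text (0.035 mg/kg), against 0.75 µmol/kg intravenous 2H5-Phe: ratios of about 26 and 0.27. These are amounts given a day apart, not label carried over into bacteria, and no carry-over fraction is stated. Likewise, discounting the leucine pair because spirulina might release 13C6-Leu would need the spirulina to be fully labelled, which the text does not say.

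**Conclusion.** The point holds for the D-amino-acid index. As defined, it cannot separate microbial conversion from dilution and from luminal label supply. Under the assumed fractions the supply effect alone is 2.5- to 3.5-fold; the true size cannot be derived from the documents. An association with morphometry would therefore not by itself show a difference in microbial activity.

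It would go too far to conclude that both indices are non-specific or that Aim 3 item III cannot be answered. The leakage ratio needs a clarification only: it is defined by element although the labels are separable by mass, and its 13C term moves with unabsorbed oral label. That dependence makes malabsorption look like less leakage, so it would tend to mask an association with severity rather than create one.

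Severity is low, because this is one exploratory sub-item among many Aim 3 measures.

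**What to change.** 1. Keep the labelled D concentration and add D/(D+L) within each Day 3 isotopologue: 2H5-Phe and 2H3-Leu for leaked amino acid, 13C6-Phe and 13C6-Leu for ingested amino acid. Use the fraction as the main index of conversion ability.
2. State that the fraction removes dilution but can still depend on absorption if D- and L-forms are absorbed differently.
3. State that the leakage ratio uses only these Day 3 isotopologues, excluding Day 2 2H8-Phe and label derived from deuterated water, and that its 13C term also varies with unabsorbed oral label.

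The cost is one extra derived variable per isotopologue. L- and D-forms are already assayed in the aspirate and isotopologue measurement is already planned, but the documents do not say that D and L are resolved per isotopologue in a single assay; the laboratory should confirm this.

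Separately, the amounts of Solution A differ between Table 3 and the Day 2 text (2H8-Phe 200 mg against 0.035 mg/kg; deuterated water 1 mL/kg against 1 g/kg), and the Day 3 tracer units differ between Table 3 and the text. Those passages must be reconciled; the point above does not depend on which is right.
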